### Study aims

#### Main aims

1. To evaluate the effect on the frequency of overanticoagulation of the implementation in the computerised physician order entry system of two types of tool to adjust OAT doses (one personalised and one non-personalised).

2. To assess any advantages of using the personalised tool rather than the non-personalised tool.

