## Methods

### Experimental design

The study is an alternate time series experiment which consists of three successive six-month periods (timed to change with the changing of medical residents even though they will not be the only prescribers). Each phase will consist of:

• a two-month period without active support during which evaluation criteria will be collected (period A),

• a two-month period with non-personalised active support (period B),

• a two-month period with personalised active support (period C).

To limit the impact of a learning effect on appropriate OAT management practice within the department over time (possible for medical residents), the order of these three periods was determined by using a Latin square plan (see Figure). This experimental design can be considered valid for an impact study in this context whereas a randomised controlled design is difficult to apply with just one hospital [20].

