#### Hypothesis about the efficacy of the intervention

The number of INR tests necessary for a six-month period, with an α risk of 5% and a power of 80%, for the comparison of two percentages by classical methods (untreated group half the size of the treated group), for a basal incidence of the judgement criterion of 12% are and for the following hypotheses on relative reduction of the risk (RRR) of overdose, are:

• RRR 30%: 2500

• RRR 40%: 1300

• RRR 50%: 800

• RRR 60%: 500

Carrying out approximately 5000 tests over six months will make it possible to detect an intervention effect of less than 30% in this period. The experimental design includes three six-month periods and should thus ensure adequate power.

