### Statistical analyses

Statistical analyses will be performed with the STATA statistical software (release 8, STATA corp, College station, Tex, USA)

Standard statistical tests will be used to compare the baseline characteristics of the departments and patients.

The main analysis concerns the effect of the intervention on the number of dangerously high INRs. The analysis will be carried out using a mixed effect analysis of variance model, in which the effect linked to the period will be considered fixed and that linked to the prescription tool will be considered random [22].

Rosendaal's method will be used to analyse the number of patient-days with INR over the target [21].

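### The main model makes the prescription tool a random effect, although both main aims need fixed contrasts between its three chosen levels

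*Protocol article*

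**What the plan says.** The Statistical analyses section introduces the primary comparison with "The main analysis concerns the effect of the intervention on the number of dangerously high INRs". A mixed-effect analysis of variance is the chosen model. On how its two factors enter, the section states that "the effect linked to the period will be considered fixed and that linked to the prescription tool will be considered random". The only other analysis of the outcome in that section applies Rosendaal's method to patient-days and names no comparison between tools.

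Three other places say what this analysis must answer:

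- **Main aims.** The first aim is the effect on overanticoagulation of introducing two named tools. The second is "To assess any advantages of using the personalised tool rather than the non-personalised tool".
- **Experimental design.** Each six-month phase contains three two-month conditions: A without support, B with the non-personalised tool and C with the personalised tool.
- **Hypothesis about the efficacy of the intervention.** INR numbers are given for "the following hypotheses on relative reduction of the risk (RRR) of overdose", as a comparison of two percentages with the untreated group half the size of the treated group.

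The Methods part of the abstract promises an analysis that allows for clustering by patient and by physician. The model sentence names neither.

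**The concern.** A factor is normally made random when its levels stand for a wider population and the interest lies in how much that population varies. Neither holds here. The three conditions are the ones the trial was set up to compare, one of them is the control, and the questions concern those particular levels.

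With a random tool effect, the model's parameter for the tool is a variance. Differences between tools come out as predictions pulled towards their common mean. The trial would then report attenuated differences where its aims need direct estimates with confidence intervals, both for each tool against control and for personalised against non-personalised. An analyst who noticed this and switched to a fixed effect would depart from the published main analysis, and the switch could look data-driven.

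**Working it through.** **1. The plan's own figures.** Inputs from the sample-size section: control rate 12%, alpha 5%, power 80%, one untreated to two treated. Two-sided testing is assumed because it reproduces the figures. With k = 2, p2 = 0.12 × (1 − RRR) and p̄ = (p1 + 2·p2)/3:

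n(untreated) = [1.96·√(1.5·p̄(1 − p̄)) + 0.842·√(p1(1 − p1) + p2(1 − p2)/2)]² / (p1 − p2)²

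| RRR | p2 | n untreated | total (×3) | stated |
|---|---|---|---|---|
| 30% | 8.4% | 814 | 2442 | 2500 |
| 40% | 7.2% | 429 | 1287 | 1300 |
| 50% | 6.0% | 256 | 768 | 800 |
| 60% | 4.8% | 165 | 495 | 500 |

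Each total rounds up to the stated figure. The sample size therefore already treats the comparison as a fixed difference between two percentages.

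**2. What each model gives.** Take block proportions by semester (3) and tool (3), with semester fixed. There are 9 blocks and 9 − 1 − 2 − 2 = 4 residual degrees of freedom. Let MST and MSE be the tool and residual mean squares.

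- *Tool fixed:* each contrast is a difference of two tool means, with standard error √(2·MSE/3) and a t interval on 4 df.
- *Tool random:* the tool variance is estimated as max(0, (MST − MSE)/3) on 2 df. Each tool's predicted deviation is its observed deviation times λ = max(0, 1 − MSE/MST).
- *Overall test:* F = MST/MSE under both labels when the layout is balanced.

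Within one trial, λ is the same for every tool, so it scales all three pairwise differences alike. If MST falls below MSE, λ is zero and all tools are predicted to be identical.

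A variance among three levels would also be poorly determined: even with tool means known without error, its 95% interval runs from 2/7.378 = 0.27 to 2/0.0506 = 39.5 times the estimate.

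**3. Illustrative size.** From the document: 12% control, 8.4% (12% with RRR 30%), and 2620 INRs above 2 in six months, so 2620/3 ≈ 873 per block. Assumed: the 10% rate, which tool has which rate, and extra between-block SDs of 0, 1 and 2 percentage points.

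Hand check for 12/10/8.4% (none/non-personalised/personalised), in squared percentage points:

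- Mean 10.13; deviations 1.87, −0.13, −1.73; sum of squares 6.51.
- Tool part of expected MST: 3 × 6.51/2 = 9.76.
- Binomial part of expected MSE: average p(1 − p)/873 = 0.0908/873, or 1.04.
- SD 0: 1 − 1.04/10.80 = 0.90.
- SD 1: 1 − 2.04/11.80 = 0.83.
- SD 2: 1 − 5.04/14.80 = 0.66.

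Simulation (40,000 layouts per scenario), mean predicted difference in percentage points:

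| True rates | Contrast | True | SD 0 | SD 1 | SD 2 |
|---|---|---|---|---|---|
| 12/8.4/8.4% | either tool v control | 3.6 | 3.3 | 3.1 | 2.5 |
| 12/10/8.4% | non-personalised v control | 2.0 | 1.79 | 1.62 | 1.31 |
| 12/10/8.4% | personalised v control | 3.6 | 3.22 | 2.90 | 2.36 |
| 12/10/8.4% | personalised v non-personalised | 1.6 | 1.43 | 1.28 | 1.05 |

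In the second scenario the ratio to the true difference is about 0.9, 0.8 and 0.65 for all three contrasts. The tool variance is estimated as exactly zero in about 0.2%, 4% and 19% of runs. In the first scenario this happens in about 0%, 1 to 2% and 13 to 14%.

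**The case against.** The strongest defence is that the sentence is a wording fault and not a decision to estimate a variance. The article uses *period* both for the six-month semesters and for conditions A, B and C. On the second use, the fixed period effect could already be the tool comparison, and the random term could be a slip, for example for the prescriber, whose clustering the abstract promises. The reference cited for the model is not at hand, so intent cannot be settled. This stands as an explanation. It does not remove the fault, because the sentence separately names the prescription tool as random, and an analyst following it would fit the wrong model. Nor is this a detail left to the SAP: the protocol states the model.

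A reader might also infer more than the document supports:

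- *That the direction of effect is lost.* It is not. The model gives signed predictions, only shrunken ones.
- *That the significance test fails.* In a balanced layout the overall F test is the same either way. It does not, however, say which tool differs from which, or by how much.
- *That personalised v non-personalised suffers most.* One common factor scales all contrasts. In points, the larger control contrast loses more: 3.6 to 3.22, against 1.6 to 1.43, at SD 0.
- *That a loss of a third is to be expected.* That needs the 2-point SD, which is assumed. The article describes the overdose frequency as stable over its six baseline months, which lends that case no support.

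**Conclusion.** The point holds. The main model as worded does not match the main aims, the design or the sample size, and no other part of the document states a fixed tool contrast. What is missing is a set of unshrunken contrasts with conventional confidence intervals. Shrinkage towards no difference follows from the model itself. Its amount, roughly 0.65 to 0.9 of the true differences, is illustrative and rests on the assumed block SDs of 0 to 2 percentage points, the assumed tool rates, 873 INRs per block and a balanced layout. Whether the sentence reflects intent or a slip cannot be decided from the document, and the correction is needed in either case.

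**What to change.** In the Statistical analyses section:

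1. State that the tool (conditions A, B, C) is a fixed factor with three levels and the control as reference.
2. Name the estimates to be reported: non-personalised v control, personalised v control, and personalised v non-personalised, each with a 95% confidence interval.
3. Say that *period* in the model means the six-month semester, and keep it fixed. Making the three semesters random instead would only repeat the problem of a variance estimated from three levels.
4. Use random effects for the patient and physician clustering already promised in the abstract, not for the tool.

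The cost is a sentence or two. No extra data, patients or time are needed, and the sample-size figures are unaffected. The change should be made and dated before the outcome data are analysed.

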## Regulatory aspects

According to French policy, this study was exempt from medical ethics committee approval. The anti-coagulants being evaluated are prescribed as recommended by clinical studies validated within the GPEH. These recommendations are available on the hospital's Intranet and are thus accessible to all doctors. They conform to standard practices. Neither the patients nor the doctors will be randomised. The interventions are simply different means of giving valid information to physicians. Using funding from the PHRC (Hospital Clinical Research Program), we carried out two research studies related to this project. In the first (PHRC 95), an intervention aimed at modifying the way in which emergency department doctors handle ankle injuries, the study design was a randomised controlled study and the randomisation unit was the hospital [11]. In the second (PHRC 98), a computer-based decision-support system for the prevention of venous thromboses in orthopaedics, the experimental design was identical to that of our present study [12]. In both cases, the Ile de France branch of the Clinical Research Delegation considered that the project was exempt from medical ethics committee approval.

## List of abbreviations

OAT: Oral Anticoagulant Therapy

INR: International Normalized Ratio

GPEH: Georges Pompidou European Hospital

PHRC: Hospital Clinical Research Program
